**Randomization and interventions**

Participants will be randomized using four blocks based on age and gender in 1:1 ratio into two groups using computer generated randomization (https://www.sealedenvelope.com/simple-randomiser/v1/lists) (According to Figure 2(. Allocation concealment will be performed by sequentially numbered containers.

Group 1 consists of 30 patients who will be received two curcumin-piperine capsules per day for 12 weeks (each capsule contains 500 mg curcumin and 5 mg piperine; a total of 1000 mg curcumin and 10 mg piperine per day). 

Group 2 will be the control and consists of 30 patients who will be received two placebo capsules per day (maltodextrin) (each capsule contains 505 mg maltodextrin; a total of 1010 mg of maltodextrin per day) for 12 weeks. 

Study compliance will be evaluated by giving a supplement box to the participants every month. At the end of every month, the number of unused supplements will be counted and recorded. Patients will be reminded to take supplements weekly by phone and SMS during the study. Participants will be excluded from the study if they take less than 80% of the supplements during the study.

If a patient misses a dose of the supplement, it is recommended that they take the supplement immediately after the reminder. If much time has elapsed since the allotted time for consumption one dose will be considered missing. 

**Figure 2 F2:**
[figure not shown]
Trial procedure flow sheet

**Blinding **

This study will be conducted in a double-blind context, so capsules (curcumin and placebo) will be labeled A and B by the company in similar packages. Capsules will be similar in terms of shape, size, color, and odor. Investigators, participants, laboratory staff, outcome assessors, and data analyzers will be blinded to treatment assignment until final analyses will be performed.

**Measurements and outcomes**

Demographic variables (including age, sex, marital status, smoking, medical history and history, level of education, occupation, supplementation, and medication) will be collected from all participants by completing a general information questionnaire at the beginning of the trial. Anthropometric indices (waist circumference, weight, and BMI) will be measured at the beginning and at the end of the study. Bodyweight will be measured using a digital scale (Seca scale, Germany) at approximately 0.1 kg in the morning on an empty stomach without shoes and with minimal clothing. Waist circumference and height will be measured by an inelastic meter with an accuracy of 0.1 cm.

Fasting blood samples (10 ml) will be collected at baseline and 12 weeks after intervention at 8:00 am to check blood factors. high-sensitivity C-reactive protein (hs-CRP), blood glucose, triglyceride, and renal indices (blood urea nitrogen and creatinine) using the ELISA kit, also, oxidative stress indices including total antioxidant capacity (TAC) and total oxidant status (TOS) using the colorimetric method by commercial Kiazist kits (Tehran, Iran) will be measured at the beginning of the study and repeated 12 weeks after the intervention in groups A and B (Table 1).

**Table 1 T1:** Time line and applied tests. BMI: Body mass index, WC: Waist circumference, OCTA: Optical coherence tomography angiography, hs-CRP: high-sensitivity C-reactive protein, TG: Triglyceride, BUN: Blood urea nitrogen, TAC: Total antioxidant capacity, TOS: total oxidant status

[figure not shown]

**OCTA evaluation**

The density of small blood vessels in the retina will be measured by the new, noninvasive, and useful imaging method, OCTA (optical coherence tomography angiography), by an ophthalmologist before and after the study. This imaging method uses Ophthalmic Optical Coherence Tomography System (OPTOVUE) (Germany serial number 32319R2).

OCTA is able to provide clear and relevant information about volumetric blood flow quickly. In this method, by comparing the difference in intensity or amplitude of multiple signals between consecutive scans, the movement of red blood cells in the retinal blood vessels can be observed (Kim et al., 2013; Choi et al., 2013). OCTA has a higher field of view and better image quality compared to conventional OCT. It also takes less time to scan (Schwartz et al., 2014; Spaide et al., 2015).

**Sample size**

The most important finding of this study is the effects of curcumin on the accumulation of small blood vessels in the eye area (based on OCTA findings). Due to the novelty of this evaluation method, according to the researcher's knowledge, there is no similar study in this regard. Therefore, the sample size is calculated based on fasting blood glucose in a previous study (Seyyedebrahimi et al., 2018) as follows: 

Based on 80% power, an α level of 0.05, and a potential dropout rate of 10%, 60 participants (i.e. 30 participants in each group) would be required. The formula n=2[(Z1-α/2+Z1-β)2×S2]/ Δ2=2[(1.96+0.84)^2^× (27)^2^]/ (25)^2^ was used to calculate the sample size.

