## Materials and Methods

**Trial design**

This is a randomized, placebo-controlled, double-blind, parallel-arm clinical trial performed in university hospitals affiliated of Isfahan University of Medical Sciences, Isfahan, Iran. Recruitment has started in February 2022.

Sixty patients in the age group of 30 and 65 years old, diagnosed with DR with the approval of an ophthalmologist, imaging, or CT scan will be enrolled (According to Figure 1). Patients will be randomly assigned in a 1:1 ratio into two groups: 1) Placebo capsules, each containing 505 mg of maltodextrin, two capsules/day, 2) Curcumin-piperine capsules, each containing 500 mg of curcumin and 5 mg of piperine, two capsules/day. Patients will be asked to consume capsules after breakfast and dinner for 12 weeks.

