**Statistical methods**

The present study will report quantitative variables as average (standard deviation) and qualitative variables as number (percentage). The normality of the distribution of quantitative variables will be assessed using the skewness index and the Q-Q plot diagram. Intragroup analyses will be performed using paired t-test and intergroup analyses using independent t-test and ANCOVA. The distribution of qualitative variables will be compared between the two groups using the chi-square test. SPSS software version 22 will be used to analyze the data with a significance level of p<0.05. The analysis will eventually be performed in the form of Intention-To-Treat (ITT) and Per-Protocol (PP).

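### The 80% power in the sample-size paragraph comes from a fasting-glucose calculation and is not established for OCTA vessel density, the outcome called most important; nor does 60 follow from the glucose inputs at 80%

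*Protocol article*

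**What the plan says.** All of the plan's reasoning on size is in the Sample size section of the Protocol article.

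- It names the main outcome: "The most important finding of this study is the effects of curcumin on the accumulation of small blood vessels in the eye area", assessed by OCTA. The aim at the end of the Introduction includes macular vascular density in OCTA, and the Discussion rests the trial's claim to be first on it.
- It explains why that outcome was not used for sizing: "according to the researcher's knowledge, there is no similar study in this regard".
- It substitutes another outcome: "Therefore, the sample size is calculated based on fasting blood glucose in a previous study".
- It states 80% power, an α of 0.05 and 10% dropout, and concludes that "60 participants (i.e. 30 participants in each group) would be required".
- It prints the formula with its numbers: "2[(1.96+0.84)^2^× (27)^2^]/ (25)^2^ was used to calculate the sample size". No unit is given for the 27 or the 25.

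The Statistical methods section plans "intergroup analyses using independent t-test and ANCOVA". The OCTA evaluation section provides for imaging before and after the study, so a baseline value will be available for adjustment.

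**The concern.** A power figure belongs to one outcome with one assumed difference and SD. Here it is computed for glucose and appears in a paragraph that opens by naming vessel density as what matters most. The document gives no SD, target difference or power for vessel density, and no argument that links a glucose effect to a vessel-density effect.

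What is at stake is how the OCTA result is read. The Discussion calls the intervention time relatively short and lists several limitations, but unknown power for the main outcome is not among them. A reader who carries the 80% over to OCTA would credit the trial with a sensitivity that nobody has worked out.

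The second question is whether 60 patients is an 80% design even for glucose. If it is not, simply relabelling the 80% as the glucose power would put another wrong figure in the plan.

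**Working it through.** **Inputs from the document.** Z values 1.96 (two-sided 0.05) and 0.84 (80% power); S = 27; Δ = 25; dropout 10%; 1:1 allocation; 30 per arm. Evaluable per arm after dropout: 30 × 0.9 = 27.

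**Step 1: the plan's own figure.**

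n per arm = 2 × (1.96 + 0.84)² × 27² / 25² = 2 × 7.84 × 729 / 625 = 18.29, so 19.

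Allowing for dropout: 18.29 / 0.9 = 20.3, so 21; or 19 / 0.9 = 21.1, so 22. The total is 42 to 44. The stated 60 is not reproduced. Raising the power to 90% with the same inputs gives 25 per arm, 28 with dropout and 56 in total, which is still not 60 and not the stated power.

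**Step 2: glucose power at the planned size.** Standardised difference 25/27 = 0.926. Noncentral t, two-sided 0.05:

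| Per arm | Power for the glucose inputs |
|---|---|
| 19 | 79% |
| 27 | 92% |
| 30 | 94% |

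So 80% is not the glucose power of a 60-patient trial.

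**Step 3: what the planned size can detect on OCTA.** The document gives no OCTA inputs, so results are in SD units. A detectable standardised difference needs only n, α and power, all of which the plan supplies.

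- t-test, 27 per arm, 80% power: solving the noncentral t power equation for d gives 0.777, about 0.78 SD.
- Normal-approximation check: (1.96 + 0.84) × √(2/27) = 0.76.
- ANCOVA on baseline: multiply by √(1 − ρ²), where ρ is the correlation between baseline and 12-week vessel density. No value of ρ is given, so 0.5 to 0.8 is an assumed range.

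| Analysis | Detectable at 80% power | Power if the true effect is 0.5 SD (assumed) |
|---|---|---|
| t-test | 0.78 SD | 44% |
| ANCOVA, ρ = 0.5 | 0.777 × 0.866 = 0.67 SD | 55% |
| ANCOVA, ρ = 0.7 | 0.777 × 0.714 = 0.55 SD | 71% |
| ANCOVA, ρ = 0.8 | 0.777 × 0.600 = 0.47 SD | 85% |

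The power column is the noncentral t with 27 per arm and standardised effect 0.5/√(1 − ρ²). The last row passes 80%, so the OCTA power can fall on either side of the stated figure, depending on quantities that the plan does not give.

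**The case against.** The strongest reply is that the plan hides nothing. The sentence before the 80% says that the calculation is for glucose and gives the reason. The paragraph makes no explicit claim of OCTA power, and a careful reader would not assume one. This stands in part: there is no concealment, and misreading is a risk rather than a certainty. But the reason given explains only why no OCTA estimate was borrowed. It does not supply power for OCTA, and it did not prevent the authors from stating a detectable difference in SD units.

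Three stronger readings are tempting, and the documents do not support them.

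- *That the trial is underpowered for OCTA.* With no OCTA SD, target difference or baseline correlation, power is unknown; it has not been shown to be below 80%.
- *That vessel density would have to move by 0.93 SD.* That is the ratio of the glucose inputs and corresponds to roughly 19 to 20 per arm. The planned size detects less: 0.78 SD unadjusted, and smaller with adjustment.
- *That only a very large effect could be seen.* ANCOVA is planned and OCTA is measured at both times. At an assumed correlation of 0.8 the detectable difference is 0.47 SD.

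How confidence intervals will be reported and how a non-significant result will be worded can reasonably be left to the full protocol or analysis plan. Neither forms part of this point.

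**Conclusion.** The point holds in a limited form. The 80% is not established for the outcome that the plan calls most important, and it is not the glucose power at 60 patients either.

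The glucose part follows from the plan's own numbers: 42 to 44 patients in place of 60 at 80% power, or about 92 to 94% power at 27 to 30 per arm. The OCTA part follows from the absence of any OCTA input. The detectable differences of 0.78 SD (t-test) and 0.67 to 0.47 SD (ANCOVA) rest on 27 evaluable per arm, two-sided 0.05, equal variances and assumed correlations of 0.5 to 0.8. The 0.5 SD effect is illustrative and is not a prediction.

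The correction should be made because the paragraph is the plan's only statement on power and is inaccurate for both outcomes. It does not call the design or the number of patients into question.

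**What to change.** Keep 60 patients and rewrite the Sample size paragraph to say that:

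1. The calculation was made for fasting glucose with Δ = 25 and SD = 27, with the unit given.
2. Either these inputs need 19 per arm at 80% power (42 to 44 in total with 10% dropout) and 60 was chosen above that, or 60 patients give about 92% power for glucose with 27 evaluable per arm (94% with all 30). If other inputs led to 60, state those.
3. No 80% power is claimed for OCTA vessel density.
4. With 27 evaluable per arm and two-sided 0.05, the OCTA difference detectable with 80% power is about 0.78 SD by t-test, or about 0.67 to 0.47 SD by baseline-adjusted ANCOVA at assumed baseline correlations of 0.5 to 0.8. For an assumed 0.5 SD effect, power is about 44% by t-test and 55 to 85% by ANCOVA over that range.

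The cost is one paragraph. No patients, visits or procedures change, so it can be done although recruitment began in February 2022. The downside is that the figure shown for the main outcome becomes less favourable than the 80% now printed.

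### The printed sample-size formula gives 19 per group, or 22 with 10% dropout, not the 30 per group stated as required at 80% power

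*Protocol article*

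**What the plan says.** The Sample size section of the protocol article names the OCTA finding on small retinal vessels as the most important one. It reports that no similar study was known, and so "the sample size is calculated based on fasting blood glucose in a previous study". The design values come next: "Based on 80% power, an α level of 0.05", and then "a potential dropout rate of 10%, 60 participants (i.e. 30 participants in each group) would be required". The section closes with the calculation, "n=2[(Z1-α/2+Z1-β)2×S2]/ Δ2=2[(1.96+0.84)^2^× (27)^2^]/ (25)^2^ was used to calculate the sample size".

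The result of that expression is not printed. The section gives no other reason for 30 per group, such as rounding up, a wider allowance for loss, or a margin for the OCTA outcome.

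**The concern.** The article ties 60 participants directly to 80% power, alpha 0.05, 10% dropout and a fully filled-in formula. A reader can evaluate that formula in one line, and it does not lead to 30 per group.

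This is the only power statement in the article, and it is the justification for enrolling 60 people. If the printed inputs are right, 60 is not the number required. If 60 is right, at least one of the printed power, difference, SD and dropout rate is not the value that was used. Either way, the reader cannot tell from this paragraph what effect the trial was planned to detect, or with what power.

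**Working it through.** **Inputs, all from the Sample size section.** Power 80% (Z = 0.84); alpha 0.05, two-sided (Z = 1.96); SD 27; difference 25; dropout 10%; stated size 30 per group. The section prints no unit for 27 and 25. I take mg/dl, the unit used for fasting glucose under Inclusion criteria.

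**The plan's own formula.**

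n = 2 × (1.96 + 0.84)² × 27² / 25² = 2 × 7.84 × 729 / 625 = 18.29, so 19 per group (38 in total).

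**Dropout of 10%.** 19 / 0.9 = 21.1, so 22 per group and 44 in total. Multiplying instead, 19 × 1.1 = 20.9, so 21 per group.

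**Against the stated size.** 60 − 44 = 16 participants; 16 / 44 = 36% more.

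**Other readings tried, per group:**

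| Reading | Before dropout | With 10% dropout |
|---|---|---|
| Printed formula, 80% power | 19 | 22 |
| Exact t-test, 80% power | 20 | 23 |
| Exact t-test with worst-case rank-test efficiency 0.864 | 20 / 0.864 = 23.1 | 23.1 / 0.9 = 25.7, so 26 |
| One-sided alpha 0.05, 80% power | 15 | 15 / 0.9 = 16.7, so 17 |
| Printed formula, 90% power | 25 | 28 |
| Exact t-test, 90% power | 26 | 29 |
| Printed formula, 95% power | 31 | 35 |

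No reading at 80% power and 10% dropout reaches 30. The 90% rows come close, but they conflict with the stated 80% and with the printed 0.84. To get from 19 to 30 by dropout alone, the loss would have to be 1 − 19/30 = 37%.

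**What 60 delivers on the printed inputs.** The standardised difference is 25 / 27 = 0.926.

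| Evaluable per group | Power, normal | Power, t-test |
|---|---|---|
| 19 | 81.4% | 79.3% |
| 20 | 83.3% | 81.4% |
| 22 | 86.7% | 85.1% |
| 27 (30 less 10%) | 92.5% | 91.6% |
| 30 | 94.8% | 94.1% |

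**What would make 27 evaluable per group the 80%-power size:**
- With SD 27, the difference would be √(2 × 7.84 × 729 / 27) = 20.6 mg/dl. By the exact t-test it is 0.777 × 27 = 21.0 mg/dl.
- With difference 25, the SD would be √(27 × 625 / (2 × 7.84)) = 32.8 mg/dl.

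These last values show the size of the gap. They are not evidence of what was actually used.

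**The case against.** The strongest reply is that the discrepancy does no harm. On the printed inputs, 60 participants exceed the need, so at least 80% power for fasting glucose is met with room to spare. By the t-test, 20 evaluable per group are enough, so a third of each group could be lost before power fell below 80%. No endpoint, analysis or enrolment target has to change. This stands, and it makes the point a correction to the text rather than a fault in the design.

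A second reply is that a journal article condenses a fuller protocol, where a rounding-up or margin step might be written down. That is possible, but it does not settle the matter. The article itself says that 60 is required under the stated power and dropout, and that statement disagrees with the formula beside it.

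A reader might go further and infer that the printed difference or SD must be wrong, so that the trial was planned for a different effect. The documents do not support that. The printed power could equally be the misprint, since the exact t-test at 90% power gives 29 per group with dropout, one short of 30. The source of the 25 and 27 is a cited study that is not at hand.

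A reader might also infer that the trial is underpowered. For fasting glucose the arithmetic shows the opposite. For OCTA vessel density it shows nothing either way.

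**Conclusion.** The mismatch is real and can be checked from the Sample size section alone: 22 per group (44 in total) from the printed formula and dropout rate, against 30 per group (60 in total) stated as required. The article does not show which of power, difference, SD, dropout or size is in error.

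It should be fixed, but it does not threaten the trial. The figure of about 92% power assumes a true difference of 25 mg/dl, a common SD of 27 mg/dl, a two-sided t-test at 0.05 and exactly 10% loss. Per-protocol numbers could be lower, because the Exclusion criteria remove participants for intake below 80%, for any adverse event, or for a change in other treatments.

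**What to change.** Keep 60 and rewrite the paragraph in one of two ways:

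- If other values were used, print the power, difference, SD or dropout rate that actually leads to 30 per group, with the result of the formula.
- If the printed values are right, state that the formula gives 19 per group and 22 with 10% dropout, and that 60 was chosen with a margin. Then give what 60 provides: about 92% power by t-test for a 25 mg/dl difference at SD 27 with 27 evaluable per group, or 80% power for about 21 mg/dl.

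In either case, say that the power applies to fasting blood glucose only and depends on loss of no more than 10%, and that it makes no claim about the OCTA vessel-density outcome.

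The cost is one corrected paragraph, with no change to enrolment, procedures or analysis.

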**Safety**

In previous studies, no significant risk was observed during supplementation with curcumin, even at doses above 8 g/day (Mirzaei et al., 2017). However, if any adverse side effects are reported after taking, the supplements will be stopped immediately.

**Ethics approval**

The scientific code of this clinical trial is 3400358, the ethical code is IR.MUI.RESEARCH.REC.1400.253, and the IRCT code is IRCT20201129049534N5. Written consent will be received from all patients participating in the study. 

**Statistical methods**

The present study will report quantitative variables as average (standard deviation) and qualitative variables as number (percentage). The normality of the distribution of quantitative variables will be assessed using the skewness index and the Q-Q plot diagram. Intragroup analyses will be performed using paired t-test and intergroup analyses using independent t-test and ANCOVA. The distribution of qualitative variables will be compared between the two groups using the chi-square test. SPSS software version 22 will be used to analyze the data with a significance level of p<0.05. The analysis will eventually be performed in the form of Intention-To-Treat (ITT) and Per-Protocol (PP).

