**Participants **

**Inclusion criteria**

Inclusion criteria are 30 to 65 years of age, diagnosis of DR with the approval of an ophthalmologist, imaging, CT scan or PCR, and definitive diagnosis of diabetes by a diabetic physician (fasting blood glucose above 126 mg/dl, measured twice, or HbA1C greater than or equal to 6.5%).

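### Two between-group tests are planned with neither named as deciding, alongside within-arm tests that do not compare treatments

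*Protocol article*

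**What the plan says.** The Statistical methods section of the protocol article gives the whole plan for continuous outcomes in one sentence: "Intragroup analyses will be performed using paired t-test and intergroup analyses using independent t-test and ANCOVA". It sets one significance level, p<0.05. It does not rank the two between-group tests, say whether the t-test is on week-12 values or on change, list the ANCOVA covariates, or say what the paired tests are for.

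Three other places bear on this:

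- Randomization and interventions: "Participants will be randomized using four blocks based on age and gender in 1:1 ratio into two groups". The wording could mean four strata or blocks of size four. Either way, age and gender are factors in the allocation.
- Measurements and outcomes, and OCTA evaluation: anthropometry, blood markers and vessel density are all measured before and after treatment, so a baseline value exists for every outcome.
- Sample size: vessel density is called the most important finding, but "the sample size is calculated based on fasting blood glucose in a previous study".

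**The concern.** Two between-group tests on the same data give two p-values. If neither is named in advance as deciding, the more favourable one can be reported. Blinding the data analysers does not remove this, because the plan itself permits both tests.

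The two tests also differ in quality. A t-test on week-12 values uses neither the baseline value nor the allocation factors. ANCOVA can use both.

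The paired tests answer a different question: whether an arm changed over time. A significant change on curcumin beside a non-significant one on placebo is not evidence of a treatment difference, and two-arm trials with planned within-arm tests are easily read that way.

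**Working it through.** **Inputs from the Sample size section.** Two-sided α 0.05, 80% power, 10% dropout, Δ = 25, S = 27, 30 per arm. Completers: 30 × 0.9 = 27 per arm.

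**Inputs not in the documents, hence assumed.** Baseline/week-12 correlation ρ from 0.3 to 0.8; share of variance explained by age and sex from 5% to 30%; any change shared by both arms; any effect size for vessel density. S is taken as the SD of the week-12 value, because the article does not say which SD it is.

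**The plan's own figure.** The formula gives 2 × (1.96 + 0.84)² × 27² / 25² = 2 × 7.84 × 729 / 625 = 18.29, so 19 per arm. With 10% dropout, 19 / 0.9 = 21.1, so 22 per arm and 44 in total. The stated 60 is not reproduced. That is a separate matter; here it only means that 27 per arm exceeds what the stated glucose inputs need.

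**1. Open choice of test.** Simulated with no treatment effect and 27 per arm (400,000 trials per row). Each test alone holds about 5%.

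| ρ | t-test on week-12 value or ANCOVA significant |
|---|---|
| 0.3 | 6.4% |
| 0.5 | 7.3% |
| 0.7 | 8.2% |
| 0.8 | 8.7% |

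Runs of 40,000 trials gave 6.3%, 7.2%, 8.1% and 8.5% to 8.9%, which agrees apart from simulation error. If a change-score t-test is allowed as a third option, the figure is 9.0% to 9.9% (ρ 0.3 to 0.7). None of this counts the further choice between the ITT and PP results.

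**2. Power at the protocol's glucose inputs.** ANCOVA multiplies the SD by √(1 − ρ²). The unadjusted standard error is 27 × √(2/27) = 7.35.

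- t-test on week-12 values: 25 / 7.35 = 3.40; 3.40 − 1.96 = 1.44; power 92.5% (91.6% by noncentral t).
- ANCOVA, ρ = 0.3: 3.40 / 0.954 = 3.57; power 94.6%.
- ANCOVA, ρ = 0.5: 3.40 / 0.866 = 3.93; power 97.5%.
- ANCOVA, ρ = 0.7: 3.40 / 0.714 = 4.76; power 99.7%.

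The difference detectable with 80% power is 20.6 unadjusted, and 19.6, 17.8 and 14.7 with ANCOVA.

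**3. Illustration at a smaller effect.** For an assumed 0.5 SD effect (noncentral t, 27 per arm), a week-12 t-test has 44% power. A change-score t-test has 64% at ρ = 0.7. ANCOVA has 55%, 71% and 85% at ρ = 0.5, 0.7 and 0.8. No planned outcome has a documented effect of 0.5 SD; the only documented one is 25/27 = 0.93 SD.

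**4. Leaving out the allocation factors.** Simulated with four equal balanced strata and 28 per arm. If the strata explain 5% to 30% of the variance, the unadjusted test has a type I error of 4.3% down to 1.9%, while the stratum-adjusted test stays at about 5%. At 25/27 SD, power is 93.0% to 95.6% unadjusted and 93.7% to 98.3% adjusted. The unadjusted test is therefore conservative and loses some precision.

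**5. Paired tests with no treatment effect.** If each arm's paired test is significant with probability p, curcumin alone is significant with probability p(1 − p).

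- No shared change: 0.05 × 0.95 = 4.75%.
- Shared change of 0.3 SD: p = 0.245, 0.324, 0.491 and 0.660 at ρ = 0.3, 0.5, 0.7 and 0.8, giving 18.5%, 21.9%, 25.0% and 22.4%.
- Shared change of 0.5 SD: 24.6%, 20.8%, 9.2% and 2.3% at the same correlations. The figure falls once both arms are nearly always significant.

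**The case against.** The strongest reply is that this is a condensed article, ANCOVA is already in it, and the covariates may be given in a document not shown. That is fair, and it disposes of several stronger readings that a reader might infer.

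- **That the analysis ignores age and sex.** Not supported. The ANCOVA covariates are unnamed and may include both. Only the t-test necessarily leaves them out.
- **That leaving out the allocation factors yields false positives.** The effect runs the other way: the test becomes conservative.
- **That the trial loses much of its power, for example 44% against 71%.** This needs the t-test to decide, to be run on week-12 values, and an effect of 0.5 SD. The documents state none of these.
- **That glucose must fall in both arms by regression to the mean because patients enter on "fasting blood glucose above 126 mg/dl, measured twice".** That phrase is part of a diagnostic definition of diabetes, with HbA1C as an alternative. The trial's baseline sample is drawn separately, nothing says the diagnostic values are recent, and uncontrolled diabetes is excluded. A shared fall is possible but not established.
- **That efficacy will be claimed from the paired tests.** The article labels them intragroup and attaches no efficacy conclusion to them. This is a risk, not a stated intention.

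It can also be said that the article does not assign tests to outcomes, so the independent t-test might be meant for baseline comparisons. The text does not exclude this, but it does not say so either. As written, both tests serve the intergroup analyses.

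What stands is narrow. The absence of a covariate list is not the fault. The fault is that the article fixes two between-group tests at one threshold and lets neither decide.

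**Conclusion.** The point holds in this limited form. With no deciding test named, claiming success on either raises the type I error from 5% to about 6.4% to 8.7%, assuming 27 completers per arm, a t-test on week-12 values, a baseline-adjusted ANCOVA and correlations of 0.3 to 0.8. This inflation is modest and avoidable.

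Power is lost only if the t-test decides. The loss is then about 2 to 7 percentage points at the protocol's glucose inputs (correlation 0.3 to 0.7), and unknown for vessel density. The within-arm tests contribute nothing to the treatment comparison and can mislead. How often depends on a shared change that the documents neither state nor rule out.

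**What to change.** In the Statistical methods section, state before unblinding that:

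- the single deciding between-group analysis for each continuous outcome is ANCOVA of the week-12 value on treatment, the baseline value of that outcome, age and sex, reported as an adjusted difference with 95% CI;
- the independent t-test is kept only as a labelled sensitivity analysis, saying whether it uses week-12 values or change;
- within-arm changes are reported descriptively, as mean and SD, and no efficacy conclusion is drawn from them.

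The cost is a change of wording and three degrees of freedom for the covariates: 54 − 2 = 52 becomes 49 with 27 per arm. In the 0.5 SD illustration at correlation 0.7, using 49 degrees of freedom instead of 52 moves ANCOVA power from 71.4% to 71.3%. No extra patients, visits or measurements are needed.
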